### Diagnosing early-stage Parkinson’s disease

1.3

Recognizing the high cost of PD treatment as the disease progresses, a key management strategy needs to be the early identification of PD cases. An accurate clinical diagnosis of PD at the earliest possible stage is essential to timely and effective management and optimal long-term outcomes for patients (29). Among non-specialist clinicians, however, low levels of diagnostic accuracy have been reported ranging from 65% to 93%, especially when evaluating early-stage PD (30, 31). A recent systematic literature review highlighted that diagnostic accuracy of PD among general practitioners in the primary care setting is hard to ascertain as there are no well-conducted studies. However, the studies identified in the review did reveal some specific problems, such as knowledge gaps about PD and delays in referral due to lack of timely symptom identification (32). Accurate diagnosis is therefore best achieved by consultation with movement disorder neurologists; however, they are not always easily accessible, especially in LMICs, leading to delays in obtaining a definitive diagnosis and appropriate treatment (16). Misdiagnosis of PD for other types of movement disorder or other medical conditions is also relatively common among patients with early-stage disease, with rates as high as 20%–30% reported (31, 33). This is particularly evident for cases of early-onset PD, a term which describes disease occurring in people over the age of 21 but younger than 50 years of age (34) and which now accounts for 8%–10% of the PD population. However, this figure may vary across different ethnic groups due to variations in underlying genetics. Non-specialist clinicians may not be expecting what is generally perceived as a condition of the elderly, in these younger subjects. Added to this, in certain world regions, including some countries in Africa and parts of Asia, PD is associated with supernatural beliefs and sufferers may face extreme marginalization, stigmatization and persecution for having the disease, resulting in social isolation, poor attendance at healthcare facilities, lack of access to care, definitive diagnosis, and treatment (35). In the experience of the largest tertiary for PD management in Thailand, the Chulalongkorn Centre of Excellence for Parkinson’s Disease and Related Disorders (ChulaPD, www.chulapd.org) in Bangkok, PD patients are generally diagnosed when they have already had symptoms on average for 3–5 years, so they are often very symptomatic (12). Considering that dopaminergic neuron degeneration is already severe in the early stage of PD, reaching at least 60%, achieving a definitive diagnosis after several years of being symptomatic is likely to be too late. While these findings cannot be generalized to all centers in the country who see PD patients, it is possible that in less specialized institutions the situation may be even worse.

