#### Digital marker validation and data analysis

2.3.2

The eight selected markers have been developed into a digital application that has been validated as described below. Validation was undertaken in a cohort of 343 people with PD (48.6% male) and 230 control subjects (27.9% were male) without PD. Participants undertook each test activity using a mobile application and data were recorded using the built-in sensors of the mobile phone, namely the accelerometer, gyroscope, microphone, and touch screen. The validation study was approved by the Human Ethics Committee of the Faculty of Medicine, Chulalongkorn University (IRB number 0804/65). All subjects gave written informed consent before the enrolment into the study, in accordance with the declaration of Helsinki. Performance on the eight test activities were recorded by each participant using a mobile application and the built-in sensors of a smartphone, namely the accelerometer, gyroscope, microphone, and touch screen. Details of how each testing activity was performed is described in Table 5.

**Table 5 tab5:** Performance methods for each of the digital marker test activities.

Marker	Description of test
Voice vowel	Participants pronounce the sustained vowel /a/, as in “*bar*,” for 10 s without holding their breath. The test is repeated three times for each participant.
Voice sentences	Participants read sentences aloud in the Thai language, such as the example sentence “*rod tid mak loey*,” which means “*The traffic is really jammed*.” The test includes a total of 25 sentences that are commonly encountered in real-life situations.
Resting tremor	Participants are instructed to place the mobile phone on one palm with the screen facing up and lay their hand in their lap. They are then asked to specify whether the device is on the left- or right-hand side by pressing on the screen. Finally, participants are instructed to keep their hand still, along with the device, for 20 s.
Postural tremor	Participants are instructed to hold the device and press on the screen to verify which side of the hand they are holding, then stretch out their arm and maintain that posture for 20 s.
Alternate finger tapping	Participants place the device on a flat surface. They are then instructed to use their index and middle fingers of one hand to tap on two circles that appear on the screen, alternating between the two fingers as quickly as possible while maintaining correct finger alternation within 10 s.

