##### Feature extraction

2.3.2.1

Features were extracted using Python SciPy library (142). SciPy.stats was used for statistical parameters (e.g., mean, SD, kurtosis, and skew). SciPy.signal and SciPy.fft were used for extracting time (e.g., period amplitude) and frequency domain features (e.g., harmonics and formants). The extracted features were labeled according to the participant’s group before feeding to the machine learning classifier.

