##### Ensemble learning

2.3.2.3

The validation study dataset, as with many smartphone-based studies, contains missing data. Many participants only completed subsets of available tests, with less than half completing all available tests. In addition, PD symptoms are heterogeneous, meaning that patients can manifest different onset and progression patterns. To address these challenges, an ensemble classifier voting approach was employed. With this approach, the classifiers differ only in the training set based on the test activity, while the algorithm remains the same (creating a homogeneous ensemble).

Previous studies have demonstrated the benefits of accounting for the intersubject heterogeneity of PD by either combining the activity data or classifiers to enhance classification accuracy. Schwab and Karlen (145) introduced an evidence aggregation model (EAM) that integrates four trained NN models specialized in detecting PD for each test activity (walking, voice, finger tapping, and memory). This approach aims to combine several model outputs and generate a single diagnostic score. The EAM achieved an AUC of 0.85, surpassing the PD classification achieved by a single activity with single classifiers. Prince et al. (97) implemented a multi-source ensemble learning approach that utilizes three test activities (walking, voice, and finger tapping) with combined classifiers, including single neuron, random forest, convolutional NN, and deep NN. The ensemble approach classification accuracy was 82%, outperforming single activity with single or combined classifiers for PD classification. Therefore, an ensemble approach will be used for the Parkinson’s disease risk survey data analysis.

The procedure for splitting the training and testing sets for PD classification using ensemble learning is illustrated in Figure 5. Of the 343 people with PD, 162 completed all tests, while among the 230 individuals without PD, 128 completed all tests. Data from subjects who completed all tests (denoted as data t) were divided into a 90% training set and a 10% test set. The training set was combined with the data from subjects who did not complete all tests (denoted as data r) to train a specialized model for each test.

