##### Validation results

2.3.2.5

Table 6 summarizes PD classification performance using classifiers specialized for individual activity data, measured by the mean AUC with 10-fold cross validation. PD classification using balance data achieved the highest mean (±SD) AUC of 0.88 ± 0.06. The use of voice vowels resulted in a mean (±SD) AUC of 0.82 ± 0.04, which was the lowest value.

**Table 6 tab6:** Mean area under the receiver operating characteristic curve after 10-fold cross validation for each test activity.

Activity	Mean AUC ± SD
Balance	0.88 ± 0.06
Postural tremor	0.87 ± 0.06
Dual tapping	0.86 ± 0.05
Pinch-to-size	0.85 ± 0.05
Gait	0.84 ± 0.07
Questionnaire	0.83 ± 0.04
Voice sentences	0.83 ± 0.04
Rest tremor	0.83 ± 0.06
Voice vowel	0.82 ± 0.04

Test activities are sorted by their mean area under the curve (AUC) in descending order.SD, standard deviation.

Using voice vowel and voice sentence data ROC curves for PD classification using RF with 10-fold cross validation showed mean (±SD) AUC values of 0.82 ± 0.04 and 0.83 ± 0.04, respectively (Figure 6). Using resting tremor data and postural tremor data, ROC curves for PD classification using RF with 10-fold cross validation showed mean (±SD) AUC values of 0.83 ± 0.06 and 0.87 ± 0.06, respectively (Figure 7). Using dual tapping and pinch-to-size data, ROC curves for PD classification using RF with 10-fold cross validation showed mean (±SD) AUC values of 0.86 ± 0.05 and 0.85 ± 0.05, respectively (Figure 8). Using gait and balance data, ROC curves for PD classification using RF with 10-fold cross validation showed mean (±SD) AUC values of 0.84 ± 0.07 and 0.88 ± 0.06, respectively (Figure 9).

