**Figure 9 fig9:**
[figure not shown]
Receiver operating characteristic of classifiers using gait data (left) and balance data (right).

Overall, the AUC values of the specialized classifiers ranged from 0.82 to 0.88. Balance testing achieved the highest AUC of 0.88. The ensemble classifier, which utilized a combination of questionnaire responses, voice vowels, rest tremor, gait and balance activities achieved a PD prediction accuracy of 0.9108 (Table 7). Taken together, these results confirmed the validity of the selected digital markers and the mobile application and testing system for distinguishing between subjects with and without PD.

**Table 7 tab7:** The top eight test activity combination sets achieved the highest mean accuracies when evaluated on five randomly sampled test sets.

Activity count	Activities									Accuracy of 10-fold CV test set randomly selected 5 times	
	Questionnaire	Voice sentence	Voice vowel	Postural tremor	Rest tremor	Gait	Balance	Dual tap	Pinch-to-size	Mean	SD
5	✓		✓		✓	✓	✓			0.9108	0.012357
8	✓	✓	✓	✓	✓	✓	✓		✓	0.9106	0.006148
8	✓	✓	✓	✓		✓	✓	✓	✓	0.9094	0.011908
5	✓	✓	✓	✓			✓			0.9094	0.006285
8	✓		✓	✓	✓	✓	✓	✓	✓	0.9046	0.010918
7	✓		✓	✓	✓	✓	✓		✓	0.9042	0.009391
8	✓	✓		✓	✓	✓	✓	✓	✓	0.9032	0.013221
7	✓		✓	✓		✓	✓	✓	✓	0.9018	0.008849

Activity count indicates the number of specialized classifiers used for ensemble learning.CV, cross validation; SD, standard deviation.

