## Discussion

3

This article outlines the protocol for the Parkinson’s disease risk survey in Thailand which will implement screening of the national population for early signs of PD using a digital platform. Results of validation tests have demonstrated both the validity and reliability of the digital platform that comprises a symptom questionnaire and objective tests of a range of motor tasks, for population screening in both community and hospital settings, and its ability to discriminate between people with and without signs of PD. The first field study was undertaken in Nakhon Sawan Province in January 2024 and the survey is being rolled out throughout Thailand to all citizens over the age of 40 years. Data collection from individual citizens, from further provincial field tests, and from hospital screening stations is ongoing. Data collected from the survey will be used to identify subjects who have either prodromal PD or early signs of clinical PD.

Identification of strategies that could slow the human aging process, and thereby reduce the occurrence and impact of the many chronic noncommunicable diseases, such as PD, associated with advanced age, would undoubtedly have huge societal benefits, and have therefore been the focus of considerable research.

Lifestyle interventions that have been evaluated for their positive benefits in both health and disease prevention include exercise, dietary modifications and sleep. Looking at the available evidence for the benefits of these interventions, in healthy subjects, an 8-week treatment program that included diet, exercise and sleep guidance was shown to have a positive impact on parameters of aging (148). Analysis of patterns of DNA methylation, a recognized biochemical marker of age, in participants was used to calculate their DNAmAge. The program of lifestyle interventions was associated with a statistically significant 3.23-year decrease in subjects’ DNAmAge compared with controls, a potential reversal of epigenetic age.

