In conclusion, the Parkinson’s disease risk survey digital platform offers a robust, validated method with high accuracy for national screening of the Thai population for signs of PD. This provides a window for timely intervention to minimize the number of cases that progress to clinical PD and effective early treatment of those confirmed with early PD. Large scale implementation is possible with a strong linkage between multiple stakeholders who are involved with the care of PD. These objectives align with calls from global organizations, such as the WHO, for a greater focus on preventative strategies for PD in efforts to stem the steep rise in prevalence. If implemented successfully, the Parkinson’s disease risk survey could act as a model for screening strategies for other non-communicable diseases in Thailand, and elsewhere.

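### Validity and high accuracy for community and national screening are claimed from a comparison of known PD with controls, which does not show them, least of all for early undiagnosed PD

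*Protocol article*

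**What the plan says.** The validation of the digital markers is described in section 2.3.2: "Validation was undertaken in a cohort of 343 people with PD (48.6% male) and 230 control subjects (27.9% were male) without PD". Section 2.3.2.1 shows how truth was assigned: "The extracted features were labeled according to the participant’s group before feeding to the machine learning classifier". The ensemble was tested on participants with complete data (section 2.3.2.3): "Of the 343 people with PD, 162 completed all tests, while among the 230 individuals without PD, 128 completed all tests".

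Results are given for PD against non-PD only. Table 6 lists mean AUCs from 0.82 to 0.88 ("PD classification using balance data achieved the highest mean (±SD) AUC of 0.88 ± 0.06"), and Table 7 gives 0.9108 as the highest mean ensemble accuracy. Section 2.2.3 adds an AUC of 0.92 for the questionnaire, again for PD classification. Section 2.3.2.5 ends by concluding that the markers and the application can separate subjects with PD from those without.

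The purpose of the survey is wider. Section 1.7 says it is to find undiagnosed PD, both early and more advanced, in Thai people over 40, with some hope of also finding prodromal cases. The first paragraph of the Discussion says that validity and reliability have been demonstrated "for population screening in both community and hospital settings", and the last says the platform "offers a robust, validated method with high accuracy for national screening of the Thai population for signs of PD".

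**The concern.** Accuracy measured in one case mix need not carry over to another. Known patients with marked motor signs are usually easier to separate from controls than people whose disease is just beginning. If the classifiers were built and tested mostly on the former, sensitivity in early undiagnosed disease could be well below what the pooled figures suggest. Controls enrolled as a comparison group may also differ from the unselected citizens who will be screened; the article does not say where the controls came from.

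The claim matters because the end of section 1.7 describes implementation as resting on this validated methodology. A reader planning a provincial screening station would take 0.9108 as the accuracy to expect in the field, including for early disease. Nothing reported supports that use.

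**Working it through.** **1. Evidence and claim, side by side.**

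- Sample: two groups, 343 + 230 = 573 people. Stage, duration, severity score, treatment status and age are not given for this cohort (section 2.3.2).
- Reference standard: known group membership (section 2.3.2.1).
- Results: pooled PD v non-PD (Tables 6 and 7).
- Conclusion in section 2.3.2.5: discrimination of PD from non-PD. The data address this.
- Conclusion in the Discussion: validity and high accuracy for community and national screening. No further accuracy data appear between the two. The community survey in section 2.2.2 led to a change in question 9 because of orthopaedic complaints; it supplies no accuracy estimate.

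**2. What the 0.9108 fixes.** It cannot be reproduced, because no 2×2 counts and no true positive or true negative rates (TPR, TNR) are reported. Its implications can be checked. Complete data: 162 + 128 = 290; PD share w = 162/290 = 0.559. A 10% test fold is 29 people. Assuming the tested samples keep this share,

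accuracy = w × TPR + (1 − w) × TNR, so TNR = (0.9108 − 0.559 × TPR) / 0.441.

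- TPR 0.85 gives TNR 0.988.
- TPR 0.9108 gives TNR 0.9108.
- TPR 1.00 gives TNR 0.798.

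The headline therefore does not fix sensitivity even for the pooled PD group.

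**3. What it leaves open for early cases (illustration).** Assume pooled sensitivity is 0.9108 and a fraction f of the PD cases is early. Then

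early sensitivity = [0.9108 − (1 − f) × later sensitivity] / f.

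| f (assumed) | later 0.95 | later 0.98 | later 1.00 |
|---|---|---|---|
| 0.20 | 0.75 | 0.63 | 0.55 |
| 0.50 | 0.87 | 0.84 | 0.82 |

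Under these assumptions the same headline is compatible with early-case sensitivity from about 0.55 to 0.87. Neither f nor the later sensitivity is given in the article.

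**4. Single-test AUC (illustration).** Under an equal-variance binormal model, d = √2 × Φ⁻¹(AUC), and sensitivity at 90% specificity = Φ(d − 1.2816). An AUC of 0.85 gives d = 1.466 and sensitivity 57%. If early cases lay at 75% of that distance from controls, the AUC would be 0.78 and sensitivity 43%; at 50%, 0.70 and 29%. The 75%, 50% and 90% are assumptions. The calculation concerns one test, so it does not say how far the ensemble accuracy of 0.9108 would fall.

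**The case against.** The strongest reply is that no bias has been shown. The article says only that the 343 are people with PD; that they were already diagnosed is inferred from their enrolment and labelling. Section 1.3 describes the centre's general experience, not this cohort, and warns against generalising it to other centres. It also cuts both ways: if people have symptoms for 3–5 years before diagnosis, the undiagnosed pool contains clearly symptomatic people, and sections 1.7 and 2.1 count more advanced undiagnosed cases in the target. This stands. A reader might infer that the headline accuracy has been shown to overstate performance in the target group. The documents do not support that: the expected direction is reasonable for early cases, but neither direction nor size is demonstrated.

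A second reply is that the authors disclose limits. The limitations paragraph of the Discussion says that further training is needed to improve accuracy and avoid overdiagnosis, that atypical parkinsonism needs further study, and that it is unclear how prodromal people will be classified. Flagged people are referred to a neurologist, and section 1.7 presents the survey as an evaluation whose data will be reported later. A comparison of known cases with controls is an ordinary first step. This answers the prodromal part of the concern. It does not answer the rest: nowhere is accuracy in early undiagnosed clinical PD said to be untested, and the closing paragraph still calls the method validated for national screening.

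A third reply is that a condensed article may leave a breakdown by stage to fuller documents. That is fair, and the missing breakdown is not itself the fault. The fault is a stated conclusion that the reported design cannot carry.

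**Conclusion.** The point holds as a mismatch between conclusion and evidence. The validation supports discrimination of people labelled as having PD from controls, as section 2.3.2.5 says. It does not support demonstrated validity for community screening or high accuracy for national screening.

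For the early undiagnosed part of the target, the AUCs of 0.82–0.88 and the accuracy of 0.9108 are likely to be optimistic. That judgement assumes the 343 resemble the symptomatic patients described in section 1.3. Its size cannot be derived from the documents; the figures in steps 3 and 4 show how much the headline leaves open and are not estimates of the bias. The two claims are wrong as written and should be corrected whatever a stratified analysis would show.

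**What to change.** 1. Reword the first and last paragraphs of the Discussion along these lines: *the platform discriminates people with known PD from controls; accuracy for community screening and for early undiagnosed PD is not yet established, pending neurologist-confirmed field data*. This costs only the wording.

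2. Add the same statement to the limitations paragraph, which at present covers prodromal and atypical cases but not early clinical PD. Because the referral described there is for people the model flags, confirmation among them alone would give the proportion of flags confirmed, not sensitivity; the sentence should say which quantity is awaited.

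3. Where disease duration, stage or treatment status is recorded for the 343, report cross-validated AUC, TPR and TNR by these factors with intervals, as a supporting analysis. The article does not say whether they were recorded; if not, it should say that early-stage accuracy is unknown. The cost is one re-analysis, wide intervals and probably a less favourable figure. For example, if 20% of the 162 complete PD cases were early (assumption), that is about 32 people. A sensitivity of 0.70 would then carry 1.96 × √(0.70 × 0.30 / 32) = ±0.16.

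The early subset should not replace the headline. It would be imprecise, and early known patients against the same controls would still not be a community-screened sample.

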**Motor analysis**			
Tremor tests	Rest tremor (put the device on the participant’s hand while it is resting on their lap for 20 s) Postural tremor (the participant holds the device in their hand with their arm outstretched against gravity for 20 s) *Measure the tremor of both hands but one hand at the time*	[figure not shown] Rest tremor	[figure not shown] Postural tremor
Alternate finger tapping	Ask the participant to alternately tap with the index and middle fingers as fast as possible for 10 s. *Test both hands but one hand at the time*	[figure not shown]	
Pinch-to-size test	Ask the participant to pinch the finger to match the different sizes of the circle shown on the screen 5 times. *Only test the dominant hand*	[figure not shown]	
Gait test	Ask the participant to put the device in their pocket and walk straight for 3 meters, turn around and then walk back.	[figure not shown]	
Balance test	Ask the participant to put the device in their pocket and stay completely still for 15 s.	[figure not shown]	

Subjects who participate in the national screening study will be asked to give written informed consent before the enrolment in accordance with the declaration of Helsinki (IRB No.0804/65). They will be asked to complete a validated 20-item questionnaire (see below for details of its development and validation) to determine if they are experiencing any motor or nonmotor PD symptoms or if there are any signs of atypical parkinsonian disorders. They will also undertake objective tests to measure their performance on specific motor tasks, comprising spoken voice, tremor, dexterity, and mobility (see below for details of their selection and validation). Tests will be performed, and data collected, using mobile smartphone technology.

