Pinch-to-size	Participants place the device on a flat surface. They are instructed to use their thumb and index finger of one hand to pinch, following the varying size of a circle that also moved randomly across the screen. The test is repeated five times for each participant.
Gait	Participants hold the device and walk in a straight line for 3 meters, then turn around and walk back to the starting position. The route for testing is set up to indicate the walking direction and the turning point.
Balance	Participants are instructed to put the device in a pocket after pressing start to begin the test. They then stand still for 30 s. A tone is played to signify the end of the test.

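### The balance marker was validated with a start-then-pocket sequence and 30 s of standing but is deployed as 15 s, and the analysed signal may include phone handling

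*Protocol article*

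**What the plan says.** The article describes the balance test twice.

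- **Validation (section 2.3.2, Table 5).** "Participants are instructed to put the device in a pocket after pressing start to begin the test". The next sentence reads "They then stand still for 30 s", and the last reads "A tone is played to signify the end of the test".
- **Survey (section 2.1, Table 1).** "Ask the participant to put the device in their pocket and stay completely still for 15 s". No start press is mentioned.

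Section 2.3.2 says that "data were recorded using the built-in sensors of the mobile phone, namely the accelerometer, gyroscope, microphone, and touch screen". Section 2.3.2.1 describes feature extraction for all tests together: "SciPy.stats was used for statistical parameters (e.g., mean, SD, kurtosis, and skew"), with further time- and frequency-domain features taken from SciPy.signal and SciPy.fft. Section 2.3.2.5 reports that "PD classification using balance data achieved the highest mean (±SD) AUC of 0.88 ± 0.06". Balance is also ticked in every row of Table 7.

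**The concern.** Table 5 places a large movement of the device between the press that begins the test and the task being measured. The resting-tremor test in the same table also has an on-screen press, but the phone is already lying in the palm by then, so nothing comparable separates the press from the recording. For balance, the only signal to the participant that the article mentions is the one at the end. If logging runs from the press, the recording holds two activities: putting a phone in a pocket, and standing still.

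SD, kurtosis and skew are moment statistics, and a brief large transient can move all three. A classifier trained on them could use how the phone was handled as well as how the person stood. That would still be information about the participant, but it would not be balance, and it would depend on instructions and on recording length.

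The recording length does change. The classifier was trained on a test with 30 s of standing and will be applied to one described as 15 s. At stake is whether the reported AUC and accuracies describe the test that the survey uses.

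**Working it through.** **1. The two descriptions side by side**

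| | Validation (Table 5) | Survey (Table 1) |
|---|---|---|
| Start press | Yes, before pocketing | Not mentioned |
| Pocketing | After the press | Before standing still |
| Still standing | 30 s | 15 s |
| Start cue for standing | None described | None described |
| End cue | Tone | Not mentioned |

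The difference in length is explicit. A difference in handling content is possible but not stated.

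**2. The plan's own figure**

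The AUC of 0.88 ± 0.06 cannot be reproduced without the recordings. It can be checked for plausibility. With 284 PD and 201 control recordings (Table 4), the Hanley-McNeil standard error at AUC 0.88 is 0.015 overall and about 0.049 for one fold of ten (28.4 and 20.1 recordings). The stated fold SD of 0.06 is in line with that. Postural tremor has AUC 0.87 on 211 and 154 recordings, with standard error 0.018. The lead of balance is 0.01/√(0.0152² + 0.0183²) ≈ 0.4 standard errors if the two are treated as independent, so its first place is nominal. Reliance on balance is not nominal: it is in all eight Table 7 sets.

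**3. How much handling could matter, if it was recorded**

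None of the following inputs is in the article. Assume that handling takes h = 2 to 10 s before T seconds of standing, and that its RMS amplitude is r times that of sway. With f = h/(T + h), the share of signal energy due to handling is f·r²/(f·r² + 1 − f). For T = 30 s:

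| h | f | r = 1 | r = 5 | r = 10 | r at which share = 50% (√(T/h)) |
|---|---|---|---|---|---|
| 2 s | 0.062 | 6% | 63% | 87% | 3.9 |
| 3 s | 0.091 | 9% | 71% | 91% | 3.2 |
| 5 s | 0.143 | 14% | 81% | 94% | 2.4 |
| 10 s | 0.250 | 25% | 89% | 97% | 1.7 |

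If logging was delayed, or the lead-in was cut, the share is 0% in every row.

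**4. What the change from 30 s to 15 s does**

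Take h = 3 s and r = 5, again as assumptions.

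- Handling recorded in both settings: f goes from 3/33 = 9.1% to 3/18 = 16.7%, and the energy share from 71% to 83%.
- Handling recorded in validation only: the share goes from 71% to 0%.
- Handling recorded in neither: the share stays at 0%, but the length still differs. For any Fourier feature computed over the full window, the frequency spacing is 1/T, which goes from 1/30 = 0.033 Hz to 1/15 = 0.067 Hz.

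In each case the survey features would be drawn under conditions other than those used for training. The direction and size of the effect on AUC cannot be derived from the article.

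**The case against.** The strongest objection is that the article never says when sensor capture or the analysed window begins. Table 5 attaches the 30 s to standing still, which fits a timed window that opens after pocketing. Section 2.3.2.1 is a short summary for all tests, gives its features as examples, and does not say that they were computed over the whole recording. A condensed article may leave countdowns and trimming to the full protocol. All of this stands, so it cannot be asserted that handling is in the signal.

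A reader might go further and infer that handling dominates the recording, so that 0.88 measures pocketing rather than balance. The article does not support that. Handling time and amplitude are not given. A movement common to both groups raises variance in both and does not by itself produce discrimination: handling would have to differ between groups and drive the splits of the forest. The balance AUC also sits within the 0.82 to 0.88 range of the other tests and shows no sign of an artefact.

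Nor can the sex imbalance between the groups (48.6% v 27.9% male) be tied to pocket habits, for which the article gives no source. Finally, the stated conclusion is that the markers distinguish people with and without PD, not that the balance features isolate sway. A handling component would therefore be a matter of labelling and transportability, and would not refute the classification result.

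The objection does not remove the sequence that Table 5 itself sets out, or the 30 s against 15 s.

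**Conclusion.** The point holds in a limited form. Two things are documented: the validation sequence puts pocketing between the start press and the still-standing period, with no described cue or exclusion, and the validated and deployed tests differ in length by a factor of two. It follows that the balance AUC of 0.88 and the Table 7 accuracies were obtained on a recording that differs from the survey's in length and possibly in handling content.

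The size of the effect is unknown. The energy shares above run from 0% to 97% depending on assumptions that the article cannot settle, and a share of energy is not a share of discrimination. The point deserves action because balance enters every listed ensemble and the remedy uses data already in hand.

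**What to change.** 1. Reconcile Tables 1 and 5 on the length of the balance test and on the order of pressing start and pocketing.
2. State when sensor logging starts and whether the lead-in was removed before features were extracted.
3. Define the analysed window as a fixed length of still standing that opens once the phone is in place, for example after a tone. Choose a length available in both settings, and use it identically in validation and survey.
4. Re-extract the balance features from the stored validation recordings on that window, retrain, and re-report the balance AUC and the Table 7 accuracies.
5. Apply the same window to survey recordings.

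If the lead-in was already excluded, a sentence saying so settles that part, and only the length matching and the re-report remain.

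The cost is a short trimming step, a re-run on existing data and, if a tone is added, a small change to the app. A few seconds of signal are lost, and the re-reported AUC may be less favourable.
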